**Methods/Design:**

This longitudinal, quasi-experimental study is designed to demonstrate the effect of the sit-to-stand activity carried out by residents in the context of daily care with health care aides. In three intervention facilities health care aides will prompt residents to repeat the sit-to-stand action on two separate occasions during each day and each evening shift as part of daily care routines. In three control facilities residents will receive usual care. Intervention and control facilities are matched on the ownership model (public, private for-profit, voluntary not-for-profit) and facility size. The dose of the mobility intervention is assessed through the use of daily documentation flowsheets in the health record. Resident outcome measures include: 1) the 30-second sit-to-stand test; 2) the *Functional Independence Measure*; 3) the *Health Utilities Index Mark 2 and 3; *and, 4) the *Quality of Life - Alzheimer's Disease*.

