### Sampling and recruitment

Residents with dementia residing in six LTC facilities in Edmonton, and the health care aides working with them, will be recruited to participate in the study. The purposive sample of research participants will be recruited from units which serve cognitively and physically frail older adults rather than units for young disabled people or sub-acute units. Residents that have a diagnosis of dementia and are able to transfer independently, or with the assistance of one person, will be eligible for inclusion in the study. Residents with a serious physical illness or life expectancy less than six months at the time of recruitment will be excluded from the study. We expect that most of the resident participants will be recruited to the study within eight months, however recruitment will continue throughout the study if necessary.

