### Intervention group

Residents in the three intervention facilities will be exposed daily to the intervention for 6 months. This will enable an assessment of the effect of the intervention on residents' mobility over time and a preliminary assessment of the sustainability of the intervention. Their mobility, function in basic activities of daily living, and health-related quality of life will be measured at baseline, 3 months and 6 months.

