### Control group

Resident participants in the control facilities will receive usual care. The only change in their routine will be the measurement of mobility, function and health-related quality of life on three occasions as for residents in the intervention group. Health care aides may work in more than one unit in a facility thus intervention and control groups will be designated at the facility level rather than the unit level to avoid contamination of the control group. It is also possible that some health care aides may work in more than one facility. We will assess the extent of contamination of the control group at the end of the study by asking health care aides who work control facilities if they have ever encouraged residents in the control facilities to repeat sit-to-stands.

LTC facilities in the intervention group will be matched to the control group facilities on ownership model (public, private for-profit, voluntary not-for-profit) and size because quality of care and resident outcomes are associated with ownership models [49-54] and size [48,49,52]. To assess the comparability of the intervention and control facilities a research assistant will gather information about each facility by: a) interviewing managers to obtain information such as staff-to-resident ratios on each shift, availability of rehabilitation services and size of units; b) observing activity across both the day and evening shifts using a structured observation schedule; and c) measuring environments using two standardized instruments: the Alberta Context Tool and the Professional Environmental Assessment Protocol (PEAP). Drawing on data collected from the observations and data elicited during the manager interviews, total PEAP scores will be calculated immediately following each manager interview.

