The Alberta Context Tool (ACT) which measures organizational context in health care settings was developed to predict research utilization. It consists of eight dimensions that are potentially modifiable: culture, leadership, evaluation, social capital, informal interactions, formal interactions, structural and electronic resources, and organizational slack [102]. The ACT comprises 56 multiple choice items scored on five-point scales with the exception of the structural and electronic resources items scored on a six-point scale. Psychometric properties of the measure were assessed with a sample of health professionals in six Canadian pediatric hospitals [103]. A principal components analysis generated a 13 factor structure accounting for 59% of the total variance. Correlations among the 13 ACT factors ranged from 0.54 to 0.91providing evidence for internal consistency. Instrumental research utilization [103] was correlated with 12 of the 13 ACT factors at the 5% level of significance providing evidence of construct validity.

Facility level characteristics such as size of facility, size of unit and ownership model (public, private for-profit, voluntary not-for-profit) are also potential predictors of resident outcome.

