### Data Analysis

All data will be entered into an SPSS 19 database (IBM, 2010, ^©^IBM Corporation). Ten percent of the data will be double entered to assess the accuracy of data entry. We will compare the baseline characteristics of the LTC facilities, health care aides, and residents in the intervention group with the control group by computing descriptive statistics. Data are structured for each outcome measure (the 30-second sit-to-stand test; the *Functional Independence Measure*; the *Health Utilities Index Mark 2 and 3; *and, the *Quality of Life - Alzheimer's Disease*) to allow a mixed between-within subjects analysis of covariance. Specifically, the between subjects factor consists of the two groups (Control versus Intervention Group) and the within subject factor consists of the repeated measures. The covariates will include baseline characteristics the residents, including age, sex, level of cognitive impairment (Cognitive Performance Scale), extent of depression (MDS Depression Rating Scale), and extent of health instability (CHESS), and characteristics of the LTC facilities including facility size, unit size, ownership model, and quality of the environment (PEAP and ACT). A Multivariate Analysis of Covariance (MANCOVA) will be used to control the experiment-wise error rate for comparisons. Data will be analyzed according to the intention-to-treat principle, i.e. residents who relocate to another setting or who die before completing the six months of follow-up will be included in the data analysis. The extent to which the residents in the intervention facilities actually received the mobility interventions will be assessed using the documentation flowsheet measures to establish a graphical analysis of the covariate-corrected time course of performance on the mobility intervention. These analyses will be conducted using SPSS 19 in consultation with a statistician from the Centre of Health Promotion Studies at the University of Alberta.

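### The facility-level covariates are too many for six facilities: the adjusted group main effect is not estimable if size, PEAP and ACT take one value per facility, and rests on 0 to 1 degrees of freedom on the main alternative readings

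*Protocol article*

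**What the plan says.** The study covers "Residents with dementia residing in six LTC facilities in Edmonton" (Sampling and recruitment). Three deliver the intervention (Intervention group), and the abstract says "In three control facilities residents will receive usual care". Allocation does not vary within a facility: "intervention and control groups will be designated at the facility level rather than the unit level" (Control group).

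The Data Analysis section describes a mixed between-within analysis of covariance for each outcome. Group is the between-subjects factor and visit the within-subject factor. Besides age, sex, CPS, DRS and CHESS, the covariates are to include "characteristics of the LTC facilities including facility size, unit size, ownership model, and quality of the environment (PEAP and ACT"). Ownership has three categories: "ownership model (public, private for-profit, voluntary not-for-profit") (Covariates).

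Two of these factors are also used in the design: "LTC facilities in the intervention group will be matched to the control group facilities on ownership model (public, private for-profit, voluntary not-for-profit) and size" (Control group). The same section introduces PEAP and ACT as part of a comparability check in which "a research assistant will gather information about each facility by" manager interviews, structured observation and the two instruments. The article gives no rule for choosing among the facility covariates or reducing their number, and names no facility term in the model.

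**The concern.** A covariate with one value per facility is informed by the number of facilities, not by the number of residents. Group is such a variable here, so it competes with every other facility-level covariate for the information in six facilities. A list with as many parameters as facilities leaves nothing with which to judge the group effect. A list with more parameters leaves the group main effect without a unique value. The same covariate list is stated for all outcomes, so the adjusted comparison of the two groups is affected throughout.

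**Working it through.** **Sample size, for reference.** With a difference of 2, SD 3.5, two-sided α = 0.05 and power 0.80, n = 2 × (1.96 + 0.84)² × 3.5² / 2² ≈ 48.1, so 49 per group, as the Sample Size section states. That figure is not in dispute. It counts residents, and the limit below is set by facilities.

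**Inputs.** Six facilities, three per arm; group constant within facility; three ownership types (2 parameters); facility size, PEAP and ACT. Three choices favour the plan or are assumptions:
- ACT is counted as one score, although the article describes eight dimensions and names no total.
- Unit size is left out of the count, since it can differ within a facility.
- Each arm is assumed to contain one facility of each ownership type.

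**Count of facility-constant columns.** Intercept 1 + group 1 + ownership 2 + facility size 1 + PEAP 1 + ACT 1 = 7. Six facilities allow rank 6 at most. With one unit-size value per facility the count is 8.

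**The same count by matched pairs.** With one pair per ownership type, the ownership terms absorb the pair means. Group must then be learned from three within-pair differences: difference = group + b₁ × (difference in size) + b₂ × (difference in PEAP) + b₃ × (difference in ACT). That is three equations in four unknowns. Extra residents measure the three differences more precisely but do not add a fourth.

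**Numerical check.** I used 120 residents (20 per facility), the five resident covariates, and unit size varying within facility with two units per facility (assumed). Over 200 random sets of covariate values I asked whether the group contrast can be estimated.

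| Reading | Facility-constant parameters | Between-facility df | Group main effect estimable |
|---|---|---|---|
| Size, PEAP and ACT one value per facility | 7 | none | 0 of 200 |
| PEAP or ACT scored by unit, the other by facility | 6 | 0 | 200 of 200 |
| PEAP and ACT both scored by unit | 5 | 1 | 200 of 200 |
| Size equal within pairs (redundant with ownership) | 6 | 0 | 200 of 200 |
| Only two ownership types in the sample | 6 | 0 | 200 of 200 |

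Degrees of freedom are 6 minus the parameters. Combining readings can add one: PEAP and ACT by unit together with exact size matching leaves intercept, group and two ownership terms, 6 − 4 = 2.

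**Group-by-time.** I used three visits and the first row's covariates. With covariates as main effects only, the group-by-time contrasts were estimable in 200 of 200 draws. With every covariate also crossed with time, they were estimable in 0 of 200.

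**The case against.** The strongest reply is that the failure depends on coding the article does not fix. The Control group section's list of facility information includes the size of units, so it does not exclude unit-level scoring of PEAP or ACT. Size may be matched closely enough to be redundant. The effect on change is carried by group-by-time, which survives if covariates enter as main effects only. Details of coding commonly sit in a fuller plan. All of this stands, and it is why the exact failure is stated conditionally. It does not restore the model: each alternative reading taken singly leaves 0 or 1 between-facility degrees of freedom. With unit-level scores, the group estimate relies on slopes seen among units of one facility to explain differences between facilities.

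A second reply is that a study not described as randomised needs adjustment for facility environment, which the Covariates section names as a predictor of mobility loss. The aim is sound, but six facilities cannot deliver it through this list.

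A reader might go further and infer that the group effect cannot be estimated on any reading, that the trial's main answer will be arbitrary, or that software will silently drop a term. The documents support none of these. The first fails on the readings in the table. The second depends on how covariates meet time, which is not stated. The third concerns software behaviour that the article does not describe. Nor should a fixed loss of precision be quoted, because it would depend on covariate values that the documents do not give.

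**Conclusion.** The point holds in conditional form. With three ownership types and one value per facility for size, PEAP and ACT, the stated list needs at least 7 facility-level parameters from 6 facilities, and the adjusted group main effect is not estimable. Group-by-time shares the failure only if covariates are crossed with time. If PEAP or ACT is scored by unit, size is equal within pairs, or fewer ownership types are sampled, the effect is estimable but the facility level is saturated or nearly so: 0 to 1 degrees of freedom on each reading singly, and 2 where the two combined in the working apply. The listing of all these covariates is a positive statement in the article, so a fuller plan that followed it would inherit the problem.

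**What to change.** Change the covariate sentence in Data Analysis as follows.
- **Primary model:** adjust for resident-level covariates (age, sex, CPS, DRS, CHESS), take account of facility, and rely on the matching for ownership and size. Intercept and group then use 2 of 6 facility-level parameters, leaving 4 degrees of freedom. State whether covariates are crossed with time.
- **Sensitivity analyses:** one with the matched pair (6 − 4 = 2 degrees of freedom) and, at most, one with a single prespecified facility covariate (6 − 3 = 3).
- **Description:** report PEAP, ACT, facility size, unit size and staffing in the comparability check already planned.

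The cost in wording is about one sentence, and no extra data are needed. The real downside is less model adjustment for facility environment in a study not described as randomised, so residual facility-level confounding should be stated as a limitation. Six facilities cannot support the full adjustment in any case.

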### Sample Size

The sample size calculation for the number of resident participants is based on the primary outcome measure in the pilot study: the number of sit-to-stands that the resident is able to complete in 30 seconds. Based on our earlier pilot work, we observed residents' ability to maintain and in some instances increase the number of sit-to-stands that they could complete in 30 seconds. We judge an increase of two sit-to-stands completed in 30 seconds to be a meaningful change in the residents' mobility. Based on existing research [10,38,46,47] and the pilot study, the standard deviation of the 30-second sit-to-stand measure is 3.5 sit-to-stands. Thus we will need 49 residents in each of the intervention and the control groups to detect an increase in the number of sit-to-stands that the resident is able to complete in 30 seconds (power = 0.80; 2-tailed; α = 0.05). Assuming an attrition rate of 20% over 6 months we will recruit 60 residents to the intervention group and 60 residents to the control group. We expect to succeed in recruiting and following our sample of 120 residents based on our experience with the pilot study and the experience of [name] who recruited similar samples in two previous studies using similar recruitment methods [4,48].

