#### Health-Related Quality of Life

The Health Utilities Index Mark 2 and 3 (HUI2/3) is a generic health-related quality of life questionnaire based on two generic multi-attribute preference-based systems: the HUI2 and the HUI3 [69]. Interview administered versions of the HUI2/3 can typically be completed in 3 minutes [70] although other researchers report that it takes 15 to 20 minutes to administer the HUI2 to frail older adults [71]. The HUI2 assesses capacity on six dimensions (or attributes) of health status: sensation (vision, hearing, and speech), mobility, emotion, cognition, self-care, and pain. The HUI3 assesses capacity on eight attributes: vision, hearing, speech, ambulation, dexterity, emotion, cognition, and pain with each attribute consisting of five or six levels ranging from normal to severely impaired function. The HUI3 may be less prone to floor effects than the HUI2, and the HUI3 has a greater capacity to measure a wider range of utility scores than does the HUI2. Together the HUI2 and HUI3 provide complementary and clinically relevant information for LTC residents with dementia. Both have been used in samples of people with dementia [72-75]. When the HUI2 was administered to frail older adults and caregiver proxy respondents of people with dementia there was evidence of discriminant validity [76], construct validity [74] and responsiveness to decline but not responsiveness to improvement [72,74]. A change of 0.03 or more in overall HUI scores is considered clinically important as is a change in level within any of the HUI attributes [71]. The HUI2/3 was chosen over other health-related quality of life measures because its widespread use facilitates the interpretation of results and allows comparisons.

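### MANCOVA is named as the control of experiment-wise error, but it controls that error only when no outcome differs, and using it as a screen could cost the 30-second test some of the power it was sized for

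*Protocol article*

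**What the plan says.** The Data Analysis section of the protocol article lists four outcome measures: the 30-second sit-to-stand test, the FIM, the HUI Mark 2 and 3, and the QOL-AD. It plans a mixed between-within analysis of covariance for each. On multiplicity it has one sentence: "A Multivariate Analysis of Covariance (MANCOVA) will be used to control the experiment-wise error rate for comparisons". It gives no order of testing, division of alpha or closed procedure, and it does not say what follows a significant or non-significant MANCOVA.

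The Sample Size section rests on the 30-second test alone. The calculation is "based on the primary outcome measure in the pilot study", with these inputs:
- Difference: "We judge an increase of two sit-to-stands completed in 30 seconds to be a meaningful change in the residents' mobility".
- Spread: "the standard deviation of the 30-second sit-to-stand measure is 3.5 sit-to-stands".
- Error rates: "power = 0.80; 2-tailed; α = 0.05".

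The result is "Thus we will need 49 residents in each of the intervention and the control groups", raised to 60 recruited per group for attrition. No allowance is made for a multivariate test or for several outcomes. The 30-second test is called primary for the pilot study; no outcome is called primary for this trial.

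The section on health-related quality of life describes HUI2 and HUI3 as two scoring systems obtained from one questionnaire and calls them complementary.

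**The concern.** The sentence on MANCOVA is a positive claim about error control, and the method does not deliver it for separate outcomes. An omnibus test asks whether any outcome differs. If one does, the test tends to be significant, and it then offers no protection to the outcomes that do not differ.

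That situation is plausible here. The 30-second test measures the very task that residents practise, so it is the outcome most likely to move. Function and quality of life, to which the Background hypothesises that the benefit will extend, would then be exposed to false claims.

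The second part is a mismatch with the sample size. If the 30-second test may be read only after a significant MANCOVA, it must pass two tests. The calculation of 49 per group allows for one.

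**Working it through.** **Step 1. Reproduce the sample size.** Inputs from Sample Size: difference 2, SD 3.5, two-sided 0.05, power 0.80.

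n per group = 2 × (1.960 + 0.842)² × 3.5² / 2² = 48.07, rounded up to 49.

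The two-sample t test at 49 per group has power 0.80. The stated figure is right for one outcome tested alone. The standardised effect is 2/3.5 = 0.571.

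**Step 2. What MANCOVA could mean in the sentence.**
- *Screen before the separate comparisons:* it controls error when no outcome differs, and not otherwise.
- *Reported beside the separate analyses:* it puts no restriction on them and controls nothing for them.
- *The only test:* it holds 5%, but supports no conclusion on any single outcome and is not the test that the sample size assumes.

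Only the first reading limits the error of the separate comparisons at all, so it is the one to quantify.

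**Step 3. Simulate the screen.** Hotelling's T² (the two-group MANOVA test) at 0.05, followed by t tests on each outcome at 0.05; 49 independent residents per group; 40,000 trials per row. Only the 30-second test differs, by 0.571 SD. The protocol gives no correlations between outcomes, so a common correlation of 0 to 0.7 is assumed. Covariates, repeated measures and clustering by facility are left out.

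| Outcomes | Correlation | Screen significant | Power of 30-second test through screen | At least one false claim on the others |
|---|---|---|---|---|
| 4 | 0 | 0.58 | 0.57 | 0.125 |
| 4 | 0.3 | 0.67 | 0.63 | 0.122 |
| 4 | 0.5 | 0.81 | 0.72 | 0.119 |
| 4 | 0.7 | 0.96 | 0.79 | 0.108 |
| 5 | 0 | 0.54 | 0.52 | 0.150 |
| 5 | 0.3 | 0.64 | 0.60 | 0.150 |
| 5 | 0.5 | 0.79 | 0.70 | 0.146 |
| 5 | 0.7 | 0.96 | 0.78 | 0.131 |

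Five outcomes means HUI2 and HUI3 entered separately. Tested directly, the 30-second test has power 0.80 in every row. Repeat runs differ by about 0.01 at most.

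**Step 4. Check the screen analytically.** At correlation 0 the noncentrality is (49/2) × 0.571² = 8.0. The noncentral F distribution then gives a significant screen with probability 0.58 (four outcomes) and 0.54 (five), which agrees with the table. For the screen alone to reach 80% in this setting takes 76 or 82 per group before attrition.

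**Step 5. Boundary cases.**
- *No outcome differs:* the chance of any false claim through the screen is 0.03 to 0.05, so the claim of control is true here.
- *The 30-second effect is 1 SD:* the screen is almost always passed and gives practically no protection. With independent outcomes the error approaches 1 − 0.95³ = 0.143 for three others and 1 − 0.95⁴ = 0.185 for four.
- *The others improve by 0.2 to 0.3 SD:* power of the 30-second test through the screen is 0.52 to 0.75.
- *All improve by 0.571 SD:* it is 0.80 at correlation 0, falling to 0.66 (four outcomes) or 0.62 (five) at correlation 0.7.

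**The case against.** The strongest reply is that the protocol describes no screen. It does not say that a significant MANCOVA opens unadjusted 5% tests, and such follow-up rules often sit in an analysis plan that is not shown. A reader might infer that the protocol prescribes this two-step procedure and that its operating characteristics are therefore known. The text does not support that, and the figures above illustrate one reading. The statement itself still fails, because none of the three readings in the working gives the claimed control for individual outcomes.

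The size is also open to challenge. The protocol lists four instruments, not five, and nothing says that HUI2 and HUI3 both enter the MANCOVA, so the four-outcome figures come first. The correlations are assumed. Under the trial's own hypothesis that function and quality of life also improve, rejecting those null hypotheses would not be an error. The simulated tests are cross-sectional on independent residents, whereas the plan has repeated measures and covariates, and allocation is by facility. All of this stands, and it is why a range is given; neither the simulated power nor the 0.80 is this trial's actual power.

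Two further inferences go too far. One is that HUI2 should be demoted because "The HUI3 may be less prone to floor effects than the HUI2": the same section calls the two complementary and cites validity evidence for HUI2. The other is that 6 months must be the sole primary time point: outcomes are planned on three occasions, and nothing in this point requires choosing one.

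**Conclusion.** The multiplicity statement is wrong as written; this is not a detail merely left to a later document. MANCOVA controls experiment-wise error across separately analysed outcomes only when no outcome differs.

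Under the inferred screen, with a true effect of 2/3.5 SD on the 30-second test alone, the error among the other outcomes is roughly two to three times the nominal 5%. The loss of power on the 30-second test runs from about 28 percentage points to almost nil, depending on the correlations and on how many scores are entered. Power through a screen can never exceed power without it, so the direction is certain even though the size is not.

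The sample size of 49 per group is itself correct for one outcome tested alone. The fault is that the analysis section does not keep to that premise.

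**What to change.** - Name the 30-second sit-to-stand test as the primary outcome of this trial, and test its group effect at two-sided 0.05 outside any MANCOVA screen. This keeps the premise on which 49 per group was calculated.
- Make FIM, HUI2/3 and QOL-AD secondary outcomes with Holm adjustment. The smallest p-value is then compared with 0.05/3 = 0.0167, or with 0.05/4 = 0.0125 if HUI2 and HUI3 are both tested and so counted separately.
- State whether secondary claims depend on a significant primary result. If they do, error is held at 5% across all outcomes. If they do not, it is held at 5% within each of the two families, and at no more than 10% across both.
- Delete the statement that MANCOVA controls the experiment-wise error rate. A MANCOVA may still be reported as a supportive global test.

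The change needs no more residents or measurements. Its cost is the stricter threshold, and so lower power, for the secondary outcomes.

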Prior to the development of this protocol we completed a pilot study to assess the effect of the uptake of the sit-to-stand mobility intervention by health care aides on the mobility of LTC residents with dementia. This enabled us to: (1) assess the feasibility of integrating a simple activity into the daily work of health care aides; (2) develop a method of monitoring the adherence of health care aides to the activity; (3) calculate an appropriately powered sample size; and (4) begin to assess the response of this frail LTC population to the mobility intervention [34]. In the pilot study we assessed the mobility of 32 residents at baseline and after four months of exposure to the sit-to-stand intervention with the assistance of health care aides on day and evening shifts. Residents completed a mean of 29.7 (SD = 20.79; range 2 to 76) occasions of sit-to-stand repetitions in the month prior to the measurement of their sit-to-stand performance. For every 12 occasions of repeating the sit-to-stand exercise that month, the odds of improving or maintaining performance with the 30-second sit-to-stand test doubled (p = 0.02). This early finding with a small sample provides promising evidence that exposure to the sit-to-stand functional activity carried out in the context of daily care with health care aides may delay the loss of ability to transfer in nursing home residents with dementia [45]. We hypothesize that this ability to transfer will positively influence the resident's overall mobility, function and health-related quality of life.

Our research question is: What is the effect of the sit-to-stand mobility intervention on the mobility, function, and health-related quality of life of LTC residents with dementia?

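### The stated power of 0.80 is for one unadjusted test of the 30-second count and makes no allowance for the MANCOVA that is to control experiment-wise error

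*Protocol article*

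**What the plan says.** The Sample Size section says the calculation "is based on the primary outcome measure in the pilot study: the number of sit-to-stands that the resident is able to complete in 30 seconds". The inputs are a target difference ("We judge an increase of two sit-to-stands completed in 30 seconds to be a meaningful change in the residents' mobility"), a spread ("the standard deviation of the 30-second sit-to-stand measure is 3.5 sit-to-stands") and the error rates ("power = 0.80; 2-tailed; α = 0.05"). The result is "Thus we will need 49 residents in each of the intervention and the control groups", raised to 60 per group for 20% attrition. No multiplicity adjustment or multivariate test enters this calculation.

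The Data Analysis section lists the 30-second count, the FIM, the HUI2/3 and the QOL-AD, and plans a mixed between-within analysis of covariance for each. It adds: "A Multivariate Analysis of Covariance (MANCOVA) will be used to control the experiment-wise error rate for comparisons". It does not say which variables enter the MANCOVA, or in so many words that the outcome tests depend on it.

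The Background hypothesises that "this ability to transfer will positively influence" overall mobility, function and quality of life. It gives no correlations between outcomes and no expected effects on the other instruments.

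**The concern.** The test that was powered and the procedure that is to protect the conclusions are not the same. A MANCOVA controls the error rate of the separate comparisons only if those comparisons are claimed after it is significant. Under that rule the count effect has two hurdles: the multivariate test and the count's own test. The first spends numerator degrees of freedom on outcomes that may add little separation between the groups.

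If so, the trial would run in the belief that it has an 80% chance of detecting a two-stand difference when the chance under its own error control is lower. A non-significant MANCOVA could then be read as evidence of no effect on mobility.

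**Working it through.** **Inputs from the Sample Size section.** Difference 2, SD 3.5, two-sided alpha 0.05, 49 evaluable per group. Standardised effect d = 2/3.5 = 0.571, so d² = 0.3265.

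**The plan's own figure.** Normal approximation: n = 2 × (1.960 + 0.842)² / 0.3265 = 48.1, rounded up to 49. Exact noncentral t: noncentrality 0.571 × √(49/2) = 2.83 with 96 degrees of freedom gives power 0.7996. The stated figures reproduce as a single unadjusted two-group comparison.

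**MANCOVA power.** With two groups the multivariate test is Hotelling's T². For p outcomes, F has p and 2n − p − 1 degrees of freedom and noncentrality (n/2) × D², where D² is the squared Mahalanobis distance between the groups. D² cannot fall below d². It equals d² when the other outcomes add nothing given the count, that is, when each other standardised effect equals its correlation with the count times d. The noncentrality is then 24.5 × 0.3265 = 8.0.

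- p = 4 (HUI2/3 as one score): F(4, 93), power 0.580.
- p = 5 (HUI2 and HUI3 separate): F(5, 92), power 0.535.
- With the 48 per group left after 20% attrition from 60: 0.569 and 0.525.

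For a given n and SD these are floors, apart from about 0.003 if some ten covariate degrees of freedom are also spent.

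**Chance that both the MANCOVA and the count's own test are significant.** Simulated with 49 per group and at least 20,000 draws per pattern. A range in a cell is simulation error. Correlations and other effects are assumed, with one common correlation r throughout.

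| Assumed pattern | MANCOVA power, 4 / 5 scores | Both significant, 4 / 5 scores |
|---|---|---|
| Others add nothing beyond the count | 0.58 / 0.535 | 0.56–0.57 / 0.52 |
| Effect on count only, r = 0.3 | 0.67 / 0.64 | 0.63 / 0.60 |
| Others at half the effect, r = 0.3 | 0.62 / 0.58 | 0.60 / 0.56–0.57 |
| Others at half the effect, r = 0 | 0.85 / 0.87 | 0.74 / 0.74 |
| Equal effects, r = 0.5 | 0.81 / 0.79 | 0.71–0.72 / 0.70 |
| Equal effects, r = 0.3 | 0.91 / 0.91 | 0.77 / 0.77 |

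The joint chance is capped by the count's own 0.7996. It comes close to that cap only when the MANCOVA is almost certain to be significant, for example equal effects on wholly uncorrelated outcomes (MANCOVA power 0.997 or more).

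**Covariates.** If covariates explain a fraction R² of the variance and the others add nothing beyond the count, D² = d²/(1 − R²). With ten covariate degrees of freedom:

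- R² = 0.25: count alone 0.90; MANCOVA 0.72 (4 scores) or 0.68 (5).
- R² = 0.5: count alone 0.98; MANCOVA 0.89 or 0.87.

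Both tests gain and a gap remains. The document gives no R², and the Sample Size section claims no such gain. Facility clustering is a separate matter and is in none of these figures.

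**The case against.** The strongest reply is that no stated number is wrong. The 49 and the 0.80 are right for the count, and the Sample Size section claims them for nothing else. Sizing on one outcome is common, and the detail of a MANCOVA is often left to the full protocol or analysis plan. The gate and its variables are inferred from a single sentence. This stands as a limit on the point. It does not remove it, because the sentence gives the MANCOVA the job of controlling error, and it can do that job only if outcome claims depend on it.

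A reader might go further and infer that power is only 0.53 to 0.58 under the protocol's own causal hypothesis, so that a true two-stand effect would be missed almost half the time. The document does not support this. The Background hypothesis is directional. It does not say that the whole effect runs through the count, and it names ability to transfer, of which the count is one indicator. The FIM itself scores transfers and locomotion (Outcomes, Function), so it may add separation. Nor is it enough that the other outcomes are uncorrelated with the count: they must also be unaffected, since half-size effects at zero correlation give MANCOVA power of 0.85 to 0.87. The planned covariates may help too, and with R² = 0.5 the MANCOVA would pass 0.80 even in the least favourable pattern.

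MANCOVA power above 0.80 does not, however, restore the stated figure at the Sample Size inputs, because the count must still pass its own test.

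**Conclusion.** The point holds as a mismatch of scope. The 0.80 belongs to a single ungated test of the 30-second count, and the sample size makes no allowance for the planned MANCOVA. If outcomes are claimed only after a significant MANCOVA, the chance of declaring the count effect at the Sample Size inputs was 0.52 to 0.77 in the tabulated patterns. The lower end is a floor, reached when the other outcomes add nothing beyond the count.

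This rests on the gate being the intended use of the MANCOVA, on four or five scores entering it, on assumed effects and correlations, and on no covariate gain and no clustering. It is not an arithmetic error in the 49 or the 0.80, and 0.53 to 0.58 should not be quoted as the trial's power.

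**What to change.** In Sample Size, state that 0.80 applies only to the count tested on its own and not gated by the MANCOVA. Add that under such a gate the power for that effect could be as low as about 0.52 to 0.58, depending on effects and correlations that are not known.

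To keep the basis of the 0.80, change Data Analysis to a fixed sequence. Test the count first in its own analysis of covariance at 0.05. Only if that is significant, run the MANCOVA on FIM, HUI2/3 and QOL-AD at 0.05. The order matters: running the two side by side, each at 0.05, would let experiment-wise error rise to about 0.10 (1 − 0.95² = 0.0975 if independent).

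The cost is wording in two sections, with no extra residents or data. The price is that the other outcomes cannot be declared positive when the count test is not significant. If the sponsor prefers to keep the count inside the MANCOVA, the sample size should be worked for that test with stated effects and correlations. In the least favourable pattern, MANCOVA power of 0.80 needs 76 (4 scores) or 82 (5 scores) evaluable per group. At 20% attrition that is 76/0.8 = 95 or 82/0.8 = 102.5, so 103 recruited per group, against the 60 planned.
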